### Randomization and masking {16a}

Participants will be randomly allocated to either of both conditions, using the permuted block technique. An independent statistician will generate the allocation schedule without any influence of the principal investigators or therapists. Random sequence block sizes (i.e., 2, 4, and 6) will be generated using a computer random number generator with equal allocation ratio (1:1). The statistician informs the observer staff and participants of the random allocation results via email. Randomization will be computerized with a concealed randomization. Block size will be unknown to the investigators and clinicians. The randomized intervention allocation is concealed until the statistical analyses of the resulting data will be completed and outcomes will be drawn. The psychological evaluators, statisticians, and assessors who measure and record the data will be blinded to the conditions and the participants’ groups. The research team will not be able to influence the randomization sequence and will have no access to allocations. The participants will be blinded to the study hypotheses.

The data safety and monitoring committee may request unblinded data throughout the trial period, but the initial data analyses should be blinded to protect against bias in decision. The investigator must report all code breaks (with reason) as they occur on the corresponding case report form page. Unblinding should not necessarily be a reason for study discontinuation.

### Data management {19}

The data will be collected via the Internet. The participants will complete the primary and secondary outcomes at three-time points: time 1: pretreatment to allocation, including baseline (week 1); time 2: immediately after the intervention, including post-treatment assessment (week 10), and time 3: 1-month follow-up (week 14). The data will be automatically coded and depersonalized and stored on a secure server. Before recruitment, the study protocol was designed with a concentrate on ensuring data quality through standardization of data collection processes. Data collection instruments were designed with validated items. Also, instrument guides were utilized as a reference for data collectors and supervisor, which included instructions for how to use instruments, definitions, and interpretation guidelines for each question. Also, all research team members received a comprehensive refresh course in the context of psychological assessments and ethics in clinical research. The supervisor ensure that each operation will be performed to a standard.

### Confidentiality {27}

All trial-related data will be coded and depersonalized and will be securely stored using encrypted digital files within password-protected folders. The data accessibility will be limited to the principal investigator and monitoring board. Monitoring member is full professor of psychology and high experienced researcher. All data will remain confidential before and during the trial.

## Statistical methods

### Statistical methods for primary and secondary outcomes {20a}

Main analyses will be conducted on the intent-to-treat (ITT) approach, including all randomly allocated participants, regardless of attendance. The last observation carried forward (LOCF) method is one way to handle missing data. In LOCF approach, the missing data are replaced by the last observed value of that variable. The time points for the observations of missed values will be reported. Descriptive statistics will be utilized to present the continuous variables as the means and SDs and categorical variables as the numbers and percentages.

To determine whether the IMBSR is inferior to ICBT-I, the confidence interval approach was used. Non-inferiority analysis will be assessed using an *F* test statistic generated from the linear mixed model and confidence intervals [86]. This tests whether the difference between the group means is statistically larger than the non-inferiority margin (clinically significant difference) and if the upper limit of the one-sided confidence interval of the difference between the group means is less than the pre-specified margin of non-inferiority. A non-inferiority margin of 4 points on ISI is chosen for the analysis. This means that the mean difference between the groups should not be more than 4 points in favor of ICBT-I, to establish noninferiority of IMBSR. Repeated-measures analyses of variance (ANOVAs) two (condition: iMBSR *vs*. iCBT-I) × three (time point: time1, time2, time3) will be designed to compare the main treatment effects of the conditions on secondary outcomes. The values of effect sizes are presented as partial eta squared and Cohen’s *d.*

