### Sample size {14}

The sample size is calculated according to the minimal difference recommendation for non-inferiority design [85]. The minimal important difference in the severity of insomnia is a decrease of eight scores on the ISI [84]. The non-inferiority margin is half the difference (4 points on ISI). Therefore, the treatment groups will be considered equivalent if their average ISI total scores do not differ by more than 4 points. Therefore, the study will detect the minimum clinically significant difference at a one-tailed test, 5% significance level, and 80% power. Finally, 64 participants will be required. Anticipation of 25% dropout rate, the required sample size was 80. To reach the desired sample size, the link for the study will be distributed and posted on online medical staff forums. Also, the trial information will be emailed to psychologist and psychiatrist to share the trial with their clients.

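### Carrying baseline ISI forward in the intent-to-treat non-inferiority test favours the claim when dropout is similar in both arms or heavier in iCBT-I

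*Protocol article*

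**What the plan says.** The section Statistical methods for primary and secondary outcomes {20a} sets the analysis population: "Main analyses will be conducted on the intent-to-treat (ITT) approach, including all randomly allocated participants, regardless of attendance". On missing data it says "The last observation carried forward (LOCF) method is one way to handle missing data" and explains that "In LOCF approach, the missing data are replaced by the last observed value of that variable". It names no other method.

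The same section assesses non-inferiority from a linear mixed model and a confidence interval. iMBSR passes if "the upper limit of the one-sided confidence interval of the difference between the group means is less than the pre-specified margin of non-inferiority", and the margin is 4 ISI points.

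Sample size {14} works "at a one-tailed test, 5% significance level, and 80% power". It states "Finally, 64 participants will be required" and then "Anticipation of 25% dropout rate, the required sample size was 80".

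Data management {19} schedules the outcomes at baseline (week 1), after treatment (week 10) and at one-month follow-up (week 14). Eligibility criteria {10} lists missing three consecutive sessions among the exclusions. The Adherence paragraph under Outcomes {12} records modules completed and sessions attended.

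**The concern.** No ISI is scheduled between baseline and the post-treatment visit. Under LOCF, a participant without a week 10 score is therefore analysed with the baseline score, as if treatment had changed nothing. Randomisation makes baseline equal on average across arms, so with similar dropout these participants carry no expected treatment contrast and dilute the difference between arms.

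In a superiority trial that dilution works against the claim. In a non-inferiority trial a smaller difference is what the sponsor hopes to show, so it works for the claim. At stake is whether an iMBSR programme that is worse by the full margin could be declared non-inferior more often than the nominal 5%. The article's own dropout figure makes the amount of filled-in data substantial.

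**Working it through.** **Inputs from the article.** Margin 4; one-sided 5% level; 80% power; 64 evaluable participants; 80 randomised 1:1 (40 per arm); 25% dropout; ISI at baseline, week 10 and week 14.

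**Inputs assumed.** The SD, because none is stated, and the dropout split between arms.

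**1. The plan's own figure.** The figure of 64 cannot be reproduced without an SD, so I solve for the SD that yields it with a true difference of zero and 32 per arm:

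SD = 4 / [(1.645 + 0.842) × √(2/32)] = 4 / (2.487 × 0.25) ≈ 6.43.

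This is a back-solved value, so SDs of 5 and 7 are shown beside it. The 80 is 64 × 1.25. A 25% loss from 80 leaves 60.

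**2. Expected difference under LOCF.** Let iCBT-I improve by R points and iMBSR by R − 4, with dropout proportions dC and dM. Dropouts keep their baseline score, so

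expected difference = R(1 − dC) − (R − 4)(1 − dM) = 4(1 − dM) + R(dM − dC).

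With equal dropout d this is 4(1 − d), whatever R is.

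**3. False non-inferiority at a true difference of 4, equal dropout.** SE = SD × √(2/40), which is 1.44 at SD 6.43. The chance that the upper limit falls below 4 is Φ([4 − 4(1 − d)]/SE − 1.645). At d = 0.25 and SD 6.43 this is Φ(1/1.44 − 1.645) = Φ(−0.95) = 17.1%.

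| Dropout per arm | Expected difference | SD 5 | SD 6.43 | SD 7 |
|---|---|---|---|---|
| 0% | 4.0 | 5.0% | 5.0% | 5.0% |
| 10% | 3.6 | 9.9% | 8.6% | 8.2% |
| 20% | 3.2 | 17.6% | 13.8% | 12.8% |
| 25% | 3.0 | 22.6% | 17.1% | 15.7% |

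**4. Check by simulation.** The formula uses one SD for everyone, although carried-forward baseline scores have their own mean and spread. I simulated 20,000 trials per setting, comparing week 10 means. The assumptions were baseline mean 19, baseline SD 3.5, week 10 SD 6.43, correlation 0.4 and R of 6, 8 or 10. At 25% equal dropout the LOCF rate was 18.2%, 16.9% and 15.5%. Using only observed week 10 scores, with dropout unrelated to outcome, it was 4.9% in all three.

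**5. Unequal dropout, same simulation, R from 6 to 10.**

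| iCBT-I / iMBSR dropout | Expected difference | False non-inferiority |
|---|---|---|
| 35% / 15% | 2.2 to 1.4 | 36% to 51% |
| 30% / 20% | 2.6 to 2.2 | 27% to 31% |
| 20% / 30% | 3.4 to 3.8 | 11% to 7% |
| 15% / 35% | 3.8 to 4.6 | 7% to 2% |

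By the formula in step 2, the bias vanishes when R(dM − dC) = 4dM. At R = 8 that means iMBSR dropout is twice that of iCBT-I.

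**6. Power of a per-protocol set.** 25% loss leaves 30 per arm. SE = 6.43 × √(2/30) = 1.66, and power = Φ(4/1.66 − 1.645) ≈ 78%.

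**The case against.** Five points deserve weight.

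- **Loose wording on LOCF.** The sentence calls it one way of handling missing data, and the section also names a linear mixed model. Fitted to observed scores, that model would not give dropouts a zero contrast. This stands as an ambiguity. However, LOCF is the only method named and its mechanics are spelled out, so a reader would apply it. A mixed model fitted after the gaps are filled cannot undo the filling.
- **Absence of a per-protocol analysis.** A reader might infer that non-inferiority is judged on intent-to-treat alone. The article says only that the main analyses are intent-to-treat, and a supporting set could sit in a fuller document. Choosing intent-to-treat is not an error. The fault lies in pairing it with baseline carried forward for a non-inferiority limit.
- **Non-attenders.** A reader might infer that people who skip sessions also contribute no difference. LOCF does not touch anyone with an observed week 10 ISI, and any dilution there belongs to the effect of assignment. The calculation covers missing outcomes only.
- **Direction.** A reader might infer that the bias always helps iMBSR. The article points both ways. Its background cites poor adherence as a possible reason for CBT-I failure. Yet iMBSR asks for more time: 8 × 2.5 + 6 = 26 hours, against 8 × 2 = 16. If iMBSR loses clearly more, the rate is near or below nominal.
- **Visibility.** It would be wrong to say that nothing would reveal the problem. The timing of missing values, session completion and the proportion finishing are all to be reported. They would show how much is missing, but not its effect on the confidence limit.

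**Conclusion.** The concern holds as a conditional one. As written, the section leads to baseline values standing in for missing week 10 scores. With similar dropout in both arms, or heavier dropout in iCBT-I, that favours non-inferiority. At the planned 25%, equal in both arms, a true 4-point inferiority appears as 3.0. The false non-inferiority rate is then about 17% instead of 5%, or about 16% to 23% for SDs of 7 to 5.

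These figures rest on an SD that the article does not state, on equal dropout, and on LOCF being used for the primary test. The documents do not support the stronger reading that the trial is bound to favour iMBSR.

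**What to change.** In Statistical methods {20a}:

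- Drop LOCF from the primary test. Fit the linear mixed model already named to all observed ISI data from all randomised participants (the intent-to-treat set). Keep LOCF at most as a sensitivity analysis.
- Add a per-protocol analysis, defined from the attendance data already collected under Adherence and an observed week 10 ISI. Claim non-inferiority only if the upper one-sided 95% limit is below 4 in both analyses.
- Reconcile the attendance item in Eligibility criteria {10} with the inclusion of everyone regardless of attendance, by stating that participants who miss three consecutive sessions stay in outcome follow-up and in the intent-to-treat set.

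The work is one definition and one further analysis, with no new data collection. The statistical price is real. The mixed model relies on data being missing at random. The per-protocol set is open to selection bias and smaller: about 60 of 80, with power near 78% on its own at the assumed SD. Power to pass both analyses is lower still and was not computed.

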The pharmacologic treatments for insomnia have side effects and increase dependency [32]. Therefore, psychological interventions must be immediately implemented to promote the mental health of nurses exposed to COVID-19. Among non-pharmacological treatments, CBT-I is a multi-component intervention for insomnia and is recommended as first-line therapy [33]. The CBT-I addresses a wide variety of psychological issues, from modifying cognitive beliefs [34] to reducing psychiatric symptoms [35, 36]. CBT-I effectiveness for the treatment of insomnia comorbid with other disorders has been also well-documented [37–40]. Although CBT-I is a low-risk, productive, and durable treatment, some drawbacks are related to effectiveness and accessibility.

Regarding effectiveness, a significant number (30 to 40%) of insomnia patients did not respond or remit, and over half (50–60%) experienced a varying degree of insomnia symptoms following a CBT-I intervention [41]. One potential explanation is poor adherence to treatment [42]. Several core components of CBT-I (e.g., sleep restriction and stimulus control) can be difficult to implement and often result in a short-term worsening of symptoms and patient discomfort [43]. While CBT-I is effective for the treatment of insomnia comorbid with depression, this intervention may not adequately address the numerous factors that contribute to the development and maintenance of insomnia [35]. Regarding accessibility, main causes of limited access to insomnia treatments are identified. First, despite significant attempts to expand the numbers of CBT-I qualified experts the accessibility of CBT-I is still mostly restricted to clinical settings or major cities [44]. Second, the CBT-I requires a highly qualified therapist who is not geographically available. In addition to the lack of CBT-I therapists, professionals are uninformed of available therapy options. Finally, insurance payment for CBT-I may be inadequate, especially if it is provided by mental health professionals who are not physicians (such as psychologists). These barriers highlight the need for approaches that could be implemented more easily in public. Clearly, there is a need to improve and expand the available insomnia treatment options. Mindfulness-based interventions (MBIs) are additional therapies that may solve this drawback of CBT-I. A complementary and supplementary treatment, which can address the CBT-I limitations, incorporates mindfulness.

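### LOCF is the only missing-data method named for the non-inferiority analysis; it carries baseline ISI forward and, with similar dropout in both arms, can favour a non-inferiority claim

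*Protocol article*

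**What the plan says.** All references are to the protocol article.

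- **Statistical methods {20a}.** The main analyses are intention-to-treat and include everyone randomised, whatever their attendance. LOCF is introduced as one possible way of dealing with missing data and is then defined: "In LOCF approach, the missing data are replaced by the last observed value of that variable". No other method is named. The non-inferiority assessment uses an F "test statistic generated from the linear mixed model and confidence intervals". iMBSR succeeds if the upper one-sided limit for the difference is below 4 ISI points.
- **Data management {19}.** Outcomes are collected at "time 1: pretreatment to allocation, including baseline (week 1); time 2: immediately after the intervention, including post-treatment assessment (week 10"), with a third assessment at week 14.
- **Objectives {7}.** The primary comparison is at post-intervention.
- **Sample size {14}.** The test is set "at a one-tailed test, 5% significance level, and 80% power". On the margin: "The non-inferiority margin is half the difference (4 points on ISI"). On attrition: "Anticipation of 25% dropout rate, the required sample size was 80". No SD is given, and dropout is not split by arm.

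**The concern.** Baseline is the only ISI assessment before post-treatment. For the primary comparison, LOCF is therefore baseline carried forward: a participant without the post-treatment score is recorded as unchanged, in either arm.

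A block of zero-change values in both arms pulls the two means together. In a superiority trial that often works against the claim. Here the claim is that the arms differ by less than 4 points, so pulling them together works for it. At stake is the error rate of the trial's main conclusion.

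LOCF also sits awkwardly beside the mixed model. A likelihood-based mixed model can use incomplete records under missing-at-random. If LOCF fills the gaps first, that property is lost, and the filled values are treated as if they had been measured. A participant who misses week 10 but answers at week 14 would contribute a baseline value at week 10, although a later real score exists.

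**Working it through.** **Inputs from the article.** Margin 4 ISI points; one-sided 5%; 80% power; 64 participants, raised to 80 for 25% dropout; 1:1 allocation, so 40 per arm; entry ISI at least 15.

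**Assumptions (not in the article).** SD of post-treatment ISI from 4 to 6.43. Baseline mean 18 and SD 3 in both arms, with correlation 0.4 with the post-treatment score. Mean iCBT-I improvement of 8 points, with 6 and 10 also tried; 8 is taken from the article's reference change ("The minimal important difference in the severity of insomnia is a decrease of eight scores on the ISI"). Dropout is unrelated to outcome, so dropouts would have responded like completers.

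**Step 1: the plan's own figure.** With no true difference, n per arm = 2·SD²·(z₀.₉₅ + z₀.₈₀)² / 4². Setting n = 32 gives SD = 4·√(32/2) / (1.645 + 0.842) = 16 / 2.487 ≈ 6.43. The stated 64 can therefore be matched only by supplying an SD of about that size. The 80 is 64 × 1.25.

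**Step 2: shrinkage with equal dropout p.** The mean change under LOCF in each arm is (1 − p) times the completers' mean change, so the expected LOCF difference = (1 − p) × true difference. No SD is needed.

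- p = 0.25: 0.75 × 4 = 3.0. A true deficit of 5 points, beyond the margin, becomes 0.75 × 5 = 3.75, inside it.
- p = 0.10: 0.90 × 4 = 3.6.

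**Step 3: false non-inferiority at a true deficit of 4.** The LOCF variance in an arm is (1 − p)·SD² + p·3² + p(1 − p)·(mean change)². Mean changes are −4 (iMBSR) and −8 (iCBT-I). With p = 0.25 and SD 6.43:

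- iMBSR: 0.75 × 41.34 + 0.25 × 9 + 0.1875 × 16 = 36.26
- iCBT-I: 0.75 × 41.34 + 0.25 × 9 + 0.1875 × 64 = 45.26
- SE = √[(36.26 + 45.26)/40] = 1.428
- P(upper limit < 4) = Φ[(4 − 3.0)/1.428 − 1.645] = Φ(−0.945) ≈ 0.17

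A simulation of the baseline-adjusted analysis gives similar rates. At 25% missing in each arm:

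| SD | LOCF, baseline-adjusted | Observed data only, baseline-adjusted |
|---|---|---|
| 4 | 0.27 | about 0.05 |
| 5 | 0.23 | about 0.05 |
| 6.43 | 0.19 | about 0.05 |

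Over both calculations, and over iCBT-I improvements of 6 to 10 points in the unadjusted one, the range is 0.16 to 0.27. With 10% missing in each arm it is 0.08 to 0.11.

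**Step 4: unequal dropout averaging 25%.** With dropout d(C) in iCBT-I, d(M) in iMBSR and an 8-point iCBT-I improvement, the expected LOCF difference = 8·(1 − d(C)) − 4·(1 − d(M)).

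| iCBT-I / iMBSR dropout | Expected difference | False non-inferiority |
|---|---|---|
| 30% / 20% | 5.6 − 3.2 = 2.4 | 0.30–0.49 |
| 35% / 15% | 5.2 − 3.4 = 1.8 | 0.45–0.72 |
| 20% / 30% | 6.4 − 2.8 = 3.6 | 0.09–0.11 |
| 15% / 35% | 6.8 − 2.6 = 4.2 | 0.03–0.04 |

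In the last row LOCF is conservative.

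**The case against.** **The wording does not commit the trial to LOCF.** The article presents it as one option and never says that it will feed the primary test, which rests on a mixed model able to use incomplete data. This stands: a reader might infer a firm plan to run the primary test on LOCF-filled data, and the text does not go that far. It does leave LOCF as the only named and defined method, directly after the intention-to-treat statement, with its role unsettled.

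**The bias depends on what would have happened to dropouts.** If they truly stay at baseline, a completer difference of 4 with 25% unchanged in each arm is a true intention-to-treat difference of 3.0. LOCF then estimates the right mean, and the observed-data analysis, at 4.0, does not. This stands as a limit. The article gives no ground for assuming it.

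**A reader might infer that the article expects more iCBT-I dropout.** The Background offers poor adherence as one potential reason for non-response to CBT-I and says that core components "often result in a short-term worsening of symptoms and patient discomfort". It forecasts no differential attrition in this trial. The iMBSR programme is the longer one (eight 2.5-hour sessions plus a 6-hour retreat, against eight 2-hour sessions), so the opposite split is also arguable. An unqualified claim of several-fold inflation is therefore not supported.

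**Dropout is not the same as a missing ISI.** The 25% is a sample-size allowance. Assessments are online with reminders, and non-attenders remain in the analysis, so some who leave treatment may still answer. This also stands, which is why the 10% case is shown.

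**Conclusion.** The point holds in a conditional form. The article names LOCF as its only missing-data method, does not reconcile it with the mixed model, and has a visit schedule under which LOCF at the primary time point means zero change from baseline.

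With similar missingness in the two arms and dropouts who would have responded like completers, the shrinkage by (1 − p) is exact. At 25% missing, the nominal 5% error becomes roughly three to five and a half times as large; at 10% it is about double. The shrinkage does not depend on the SD. The error rates do, and they also rest on the assumed baseline values and iCBT-I improvement.

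The direction is not universal, since the dropout split can enlarge, remove or reverse the effect. That is itself a reason not to let the primary conclusion depend on LOCF: its error rate would be governed by who happens to leave which arm.

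**What to change.** 1. Remove LOCF from the primary analysis in Statistical methods {20a}.
2. State that ISI will be analysed with the likelihood-based linear mixed model already planned, on all observed values, with baseline ISI included and no single imputation. The non-inferiority limit is read from the post-treatment contrast.
3. As a cheap addition, specify a sensitivity analysis suited to non-inferiority, in which missing iMBSR values are made progressively worse (delta-adjusted or tipping-point). Report how much worse they must be before the upper limit reaches 4.

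The cost is a wording change and a little more analysis, with no extra participants or visits. The downside is that the primary model then relies on missing-at-random; the sensitivity analysis is there to examine that.

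### The non-inferiority decision mixes a valid confidence-limit rule with a reversed test, an undirected F test and criteria on the means alone; one rule should be stated as decisive

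*Protocol article*

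**What the plan says.** All statements are in the protocol article.

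**Statistical methods for primary and secondary outcomes {20a}**
- The paragraph on non-inferiority opens by naming a confidence-interval approach.
- It then says the assessment uses an F "test statistic generated from the linear mixed model and confidence intervals".
- The next sentence begins "This tests whether the difference between the group means is statistically larger than the non-inferiority margin (clinically significant difference". It goes on, joined by 'and', to require that the upper one-sided confidence limit be below the margin.
- The margin follows: "A non-inferiority margin of 4 points on ISI is chosen for the analysis". It is explained with "This means that the mean difference between the groups should not be more than 4 points in favor of ICBT-I", which the sentence presents as what establishes non-inferiority.

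**Sample size {14}**
- "The non-inferiority margin is half the difference (4 points on ISI".
- "the treatment groups will be considered equivalent if their average ISI total scores do not differ by more than 4 points".
- "the study will detect the minimum clinically significant difference at a one-tailed test, 5% significance level, and 80% power".

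**Objectives {7}** puts the non-inferiority question at post-intervention. **Primary outcome** says that higher ISI scores mean worse insomnia, so a positive difference iMBSR minus iCBT-I is a deficit for iMBSR.

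**The concern.** In a non-inferiority trial the null hypothesis is that the new treatment is worse by at least the margin, and the data must reject it. Asking whether the difference is significantly larger than the margin swaps the hypotheses: non-inferiority becomes the null, and a small or noisy trial then tends to 'pass' because it cannot show inferiority.

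An ordinary F test of the group effect asks whether the difference is zero, in either direction. It does not involve the 4-point margin unless it is shifted to it, and the article describes no shift.

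A criterion on the means alone ignores sampling error. The sample-size version also runs in both directions and is called equivalence, while the stated test is one-tailed.

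This is the trial's primary conclusion. With several wordings side by side, one set of results can satisfy one and fail another.

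**Working it through.** **1. The two clauses of the key sentence.** Let d be the estimated difference (iMBSR minus iCBT-I) and SE its standard error.
- Significantly larger than 4 at one-sided 5%: d − 1.645 × SE > 4, which needs d > 4.
- Upper one-sided 95% limit below 4: d + 1.645 × SE < 4, which needs d < 4.

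The two cannot hold together, whatever the SE. As written, the sentence describes a test that contradicts its own criterion.

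**2. False non-inferiority when the true deficit is exactly 4** (normal approximation, each wording used as the sole rule):
- Upper limit below 4: P(d < 4 − 1.645 × SE) = Φ(−1.645) = 5%.
- Means within 4: P(d < 4) = Φ(0) = 50%. The lower bound at −4 in the two-directional version changes this negligibly.
- Not significantly larger than 4: P(d < 4 + 1.645 × SE) = Φ(1.645) = 95%.

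The SE cancels, so these three figures need no SD.

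**3. An SD for illustration.** The article gives none. I solve for the one that reproduces its 64 participants (32 per arm, 1:1) with margin 4, one-sided 5%, 80% power and a true difference of zero:
- SD = 4 × √(32/2) / (1.645 + 0.842) = 16 / 2.487 ≈ 6.43.
- Check: n per arm = 2 × 2.487² × 6.43² / 4² ≈ 32, total 64.
- SE = 6.43 × √(2/32) = 6.43 × 0.25 ≈ 1.61.

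**4. What each wording would accept at SE 1.61**

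| Wording used alone | Largest d that passes | Pass rate, true deficit 4 | Pass rate, true difference 0 |
|---|---|---|---|
| Upper limit below 4 | 4 − 2.64 = 1.36 | 5% | 80% |
| Means within 4 | 4 | 50% | about 99% |
| Not significantly larger than 4 | 4 + 2.64 = 6.64 | 95% | about 100% |

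The 80% in the first row agrees with the planned power, so the sample size matches the confidence-limit rule under this SD.

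**5. One result, two answers.** Suppose iMBSR is observed to be 3 points worse. The upper limit is 3 + 1.645 × 1.61 ≈ 5.6. This fails the confidence-limit rule but meets the sample-size wording, because 3 is not more than 4. With SD 5 (SE 1.25) the limit is about 5.1, and with SD 7 (SE 1.75) about 5.9, so the conflict holds across that range.

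**The case against.** The strongest reply is that the governing method is named. The paragraph opens with the confidence-interval approach, and the upper-limit criterion, the 4-point margin, the direction and the one-tailed 5% level are all given. The clauses are joined by 'and', not offered as alternatives. If the first clause was meant as 'not significantly larger than 4', an upper limit below 4 already implies it, and the joint rule keeps its 5% error. The sentences on the means can be read as explanations of the margin, and the sample-size sentence stands beside a significance level and power, so allowance for sampling error was clearly intended.

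Much of this stands. A reader might infer that the plan has no valid rule, or that it will run with a 50% or 95% error rate. The article does not support that: the valid rule is there, and the higher rates arise only if one phrase is lifted out and used alone.

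A reader might also infer that a non-significant F test will count as success. Under the assumed SD that would pass about 30% of the time at a true 4-point deficit (11% to 37% for SD 5 to 7). The article never says so. It does not write out the F test's null, and it cites a source for the method that is not at hand; the zero null is an inference from the usual form of the test.

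What the reply does not remove is that the test is described the wrong way round, that two sentences are phrased as criteria without a confidence limit, and that 'equivalent' does not fit a one-tailed non-inferiority test.

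**Conclusion.** Wrong as written, and correctable by wording alone. The fault is a valid criterion surrounded by statements that conflict with it. The reversed clause follows directly from the text and needs no assumption. The F-test point is weaker, since it rests on the usual form of that test.

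The possible cost is a false non-inferiority rate of 50% or 95%, against the intended 5%, if the wrong phrase were applied alone. These rates are free of the SD. The example of a 3-point deficit rests on an assumed SD of 6.43, 32 evaluable participants per arm and a normal approximation, and its direction is the same for SDs of 5 to 7.

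**What to change.** In Statistical methods {20a}, state one decision rule: non-inferiority of iMBSR is concluded if the upper limit of the one-sided 95% confidence interval for the mean ISI difference, iMBSR minus iCBT-I, from the linear mixed model at post-intervention is below 4. The 95% level follows from the one-tailed 5% already stated.

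- Delete the clause on a difference significantly larger than the margin.
- Take the F test out of the non-inferiority decision; it may still be reported descriptively.
- Reword the explanatory sentence on the mean difference so that it refers to the upper confidence limit.
- In Sample size {14}, replace the sentence on equivalence with a reference to this rule.

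The cost is a wording change in two sections. Conduct, data collection and the 64 evaluable participants are unaffected.
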